### 3.4 Justification of Study Intervention

In a cRCT in the primary care setting, we successfully pilot-tested the patient-centered drug review tool, which will be used in the planned study as a component of the discharge procedure, with regard to its practicability and feasibility (32). This pilot trial has been awarded the Swiss College of Primary Care Award in 2014. At present, we are conducting a cRCT that investigates the efficacy and safety of a medication review tool fostering deprescribing in the setting of GPs in northern and central Switzerland (15). This latter study has received a grant from the SAMW (Bangerter-Rhyner foundation) and will be carried out in collaboration with the Swiss OPERAM (34) team (PI: Prof. [name], co-investigator of this project) who is currently developing a software to reduce inappropriate medication in the multimorbid elderly with polypharmacy across Europe. We think our project, focussing on communication about deprescribing in the transition

phase between hospital and ambulatory care, is complementary to the OPERAM design and fills a gap which is not addressed within the OPERAM project itself.

### **3.5 Explanation for Choice of Comparator Intervention**

The control groups' senior HPs will undergo an educative session of the same duration as their peers in the intervention group but reduced in content, merely addressing multimorbidity and how to identify eligible patients according to the in- and exclusion criteria (first two items of the list in section 8.1.1). No modifications will be made to the established discharge procedures, so both the discharging interns and the further attending physicians will follow their usual transfer routines.

In the absence of a universally standardized discharge procedure, we opted for "usual care" in the above sense as our comparator method. If the study intervention successfully proves to have a beneficial effect on the chosen outcomes then the potential superiority of the intervention will be of considerable relevance to all adopters of the intervention.

### **3.6 Risks and Benefits**

While taking a specific drug ideally has a beneficial effect on the health problem or risk factor targeted (e.g. reduction of the patient's risk of stroke) it may as well have a negative impact on other areas (e.g. adverse effects like hemorrhage, limitation of patient autonomy). In the case of polypharmacy among multimorbid patients, there is an increased risk of harmful effects on the patients' health due to the exponentially growing number of potential interactions and possible side effects (5, 9, 10, 14, 16, 22, 51).

Attempting to simultaneously adhere to both the ethical principles of care (beneficence) and precaution (non-maleficence) results in conflicting goals and requires careful risk-benefit considerations: In theory, discontinuing a drug with possible adverse effects may benefit the patient, but, on the other hand, it also means forgoing the therapeutic value of the drug with regard to the specific health condition targeted. Within the intervention of the present study, this assessment will be carried out deliberately for every single drug, and stopping a drug will only be suggested if, from a medical perspective, its (potential of already manifest) maleficent effects clearly exceed its beneficial potential. Our structured medication review process, based on a validated tool from geriatric medicine (11) and successfully tested in a pilot study (32) for an ongoing cRCT (15) encourages such considerations in the interest of patients.

Our goal is not to merely minimize the potential for harmful effects by reducing the number of drugs prescribed at hospital discharge but also to find an optimal balance between risk and benefit for the patients. To achieve this aim, our approach will favor the prioritization of indispensable and the identification of expendable medication, and the review of every single medicament together with the patient.

Of course, decisions within the deprescribing process have to be made together with the patients. The most pressing health complaints from the patients' view will guide all considerations from early stages within the medication review process. After being informed about their physicians' opinions and recommendations, the patients will then be able to decide about continuing or discontinuing any drug according to their own preferences, values and beliefs. Thus, the ethical principle of patient autonomy plays a key role in the study intervention.

Should symptoms of a previously controlled disease worsen after deprescribing, or if the activity of a disease increases in the post hospital course, then there will always be the option to revert the change and to re-introduce the original medication. In order to avoid virtually any pharmacology-related negative consequences of a deprescription, the discharging HP will be sensitized towards this problem (e.g. stepwise reduction of corticosteroids or anticoagulants).

Provided that our systematic approach will successfully prove its effectiveness in avoiding polypharmacy-induced health problems, we expect it to initiate a change in health professionals' and patients' thinking towards prioritizing, patient-centeredness, and refraining from the prescription of too many drugs for polymorbid patients. As a result, we hope to see a decrease in drug-caused health problems, medical complications, hospitalizations and unnecessary deaths, as well as a reduction in the costs entailed.

Our approach may serve as a model for an optimized discharge procedure, and we therefore expect that colleagues may welcome the suggestions in the dissemination phase. However, we also expect that a proportion of patients and caregivers may have difficulties to adopt this new kind of approach, as some barriers towards deprescribing are known from the literature (37, 42, 43, 52).

### **3.7 Study Population**

An overwhelming proportion of multimorbid patients with extensive and complex medication regimes are elderly people who are taken care of by their GPs (39). Therefore, previous studies aimed at reducing polypharmacy – including one ongoing study by the authors of this proposal – restricted their scope to geriatric patients in the primary care setting (11, 14).

But an increased risk of introducing polypharmacy emerges also at the intersection of inpatient and outpatient medicine; at discharge from hospital the prevalence of polypharmacy is dramatically higher than at hospital admission (40, 50). We therefore chose hospital HPs responsible for the patients' discharge procedures and, in particular, for their discharge medication plans as the primary recipients of our study intervention. Hospitals of all types, levels and legal structures will be considered. Given the high fluctuation among interns between different wards of many hospitals and also between different hospitals, the educative training session will normally be offered to the senior HPs who, in turn, will teach the varying interns how to apply the structured discharge procedure.

The HPs will recruit the participants from inpatients according to the relatively non-restrictive in- and exclusion criteria (see section 7.1).

Switching back to pre-hospitalization medication schemes after hospitalization has been identified as a major barrier to a lasting reduction of polypharmacy (2). Therefore, we plan to involve the GPs in the optimized discharge process by offering them the opportunity to discuss the reduced medication schemes with the responsible HPs.

## **4 STUDY OBJECTIVES**

### **4.1 Overall Objective**

Overall objective of the cluster-randomized controlled study is to investigate means and consequences of reducing polypharmacy among multimorbid hospital patients as part of an improved discharge procedure. We thus hope to contribute to a reduction of potentially inappropriate medication and adverse drug effects and ultimately help patients to a prolonged time to hospital readmission.

### **4.2 Primary Objective**

The primary objective of our project is to test the hypothesis that a simple medication review tool in combination with a defined communication strategy at hospital discharge leads to longer hospital readmission times compared to usual care (control group) and has the potential to improve the patients' health outcomes and quality of life (see secondary outcomes in section 5.2).

### **4.3 Secondary Objectives**

Secondary objectives are:

- To identify best clinical practice of how to implement this approach in the daily routine at hospital discharge
- To estimate the potential of cost savings by this approach
- To foster dissemination of this approach (if successful) among Swiss hospital wards and GPs

### **4.4 Safety Objectives**

Patient safety will be assessed by retrospectively, capturing all complications leading to GP encounters, ED visits and deaths that might possibly be related to modifications of the medication changes carried out within the study.

## 5 STUDY OUTCOMES

### 5.1 Primary Outcome

| Outcome                                                                     | Measurements                                                                                                          |
|-----------------------------------------------------------------------------|-----------------------------------------------------------------------------------------------------------------------|
| Time (days) without readmission to hospital within 6 months after discharge | Patient records tracking (patient questionnaires and/or calls, GP records, hospital records); consecutive calculation |

### 5.2 Secondary Outcomes

| Outcomes                                                                                         | Measurements                                                                                                                                                                         |
|--------------------------------------------------------------------------------------------------|--------------------------------------------------------------------------------------------------------------------------------------------------------------------------------------|
| Readmission rates at 1, 3 and 6 months after discharge                                           | Patient records tracking (patient questionnaires and/or calls, GP records, hospital records)                                                                                         |
| Number of ED visits or GP encounters within 1, 3 and 6 months after discharge                    | Patient records tracking (patient questionnaires and/or calls, GP records, hospital/ED records)                                                                                      |
| Death during follow-up of 6 months                                                               | Patient records tracking (GP records, hospital records)                                                                                                                              |
| If applicable: Reasons for readmission, ED visits, GP encounters or death                        | Patient records tracking (patient questionnaires and/or calls, GP records, hospital/ED records)                                                                                      |
| Number of drugs at discharge                                                                     | Hospital records at discharge (patient records tracking and/or calls, GP records)                                                                                                    |
| Anatomical Therapeutic Chemical (ATC) classes of the drugs prescribed/de-prescribed at discharge | Hospital records at discharge (patient records tracking and/or calls, GP records); consecutive classification at study center                                                        |
| Proportion of potentially inappropriate medications (PIMs) at discharge                          | Hospital records at discharge (patient records tracking and/or calls, GP records); consecutive classification at study center based on 2012 Beers criteria (1) and PRISCUS list (16) |
| Number of drugs at 1, 3 and 6 months after discharge                                             | Patient records tracking and/or calls (GP records)                                                                                                                                   |
| ATC-codes of the drugs prescribed at 1, 3 and 6 months after discharge                           | Patient records tracking and/or calls (GP records); consecutive classification at study center                                                                                       |
| Proportion of potentially inappropriate medications (PIMs) at 1, 3 and 6 months after discharge  | Patient records tracking and/or calls (GP records); consecutive classification at study center based on 2012 Beers criteria (1) and PRISCUS list (16)                                |
| Patients' quality of life at discharge                                                           | EQ-5D-3L-scale                                                                                                                                                                       |

|                                                                   |                |
|-------------------------------------------------------------------|----------------|
| Patients' quality of life
at 1, 3 and 6 months after discharge | EQ-5D-3L-scale |
|-------------------------------------------------------------------|----------------|

The following covariates will be used for balanced cluster allocation and subgroup analyses:

| Covariates                                                         | Measurements                                                            |
|--------------------------------------------------------------------|-------------------------------------------------------------------------|
| Patient characteristics
(age, sex)                              | Patient declaration at inclusion                                        |
| Hospital type
(A-D  ; University or Non-University) | Questionnaire/interview with decision maker
at recruitment of clinic |
| Type and size (number of beds)
of hospital clinic/ward/unit     | Questionnaire/interview with decision maker
at recruitment of clinic |

### 5.3 Process Evaluation Outcomes

| Outcomes                                                             | Measurements                                                                                                                                                                                                                                                                                                                                                                                                                                                                                                                       |
|----------------------------------------------------------------------|------------------------------------------------------------------------------------------------------------------------------------------------------------------------------------------------------------------------------------------------------------------------------------------------------------------------------------------------------------------------------------------------------------------------------------------------------------------------------------------------------------------------------------|
| HP-GP interaction/contacts with regard to
the impending discharge | HP records at discharge                                                                                                                                                                                                                                                                                                                                                                                                                                                                                                            |
| Frequency of GPs' utilization
of communication offered from HPs   | Senior HP records after inclusion of last patient                                                                                                                                                                                                                                                                                                                                                                                                                                                                                  |
| Ratings of feasibility/acceptance
among HPs                       | Questionnaires for senior HPs to be completed
after inclusion of last patient, with 5-point-Likert
scale in regard to acceptance and feasibility
among HPs, e.g.: 
 
• "The tool was well applicable in my daily work."
 
• "The tool was useful in regard to deprescribing."
 
• "I will use the tool also after the study."
 
• "I would recommend the tool to my colleagues."
 
• "The reactions of my patients to the tool were positive."
 
 |
| Barriers and enablers of deprescribing
among senior HPs           | Semi-structured telephone calls or focus group
interviews with/of senior HPs                                                                                                                                                                                                                                                                                                                                                                                                                                                    |
| Dropout rates
of HPs, GPs and patients                            | Study register data                                                                                                                                                                                                                                                                                                                                                                                                                                                                                                                |

 Clinical units of Swiss hospitals belong to one of four categories A, B, C or D, depending on their size, institution and the quality of further education provided.

The envisioned number of 42 clusters (i.e. senior HPs; see sample size calculation in section 11.2) will be randomly allocated to two equally sized trial arms by an administrative member of the study staff using a software random number generator. After the training of the senior HPs, patient recruitment will be carried out by the senior HPs themselves or on their behalf by internship physicians or nurses; a person responsible for recruitment will be designated for every participating clinic/ward. All patients recruited by an individual senior HP or his delegates (on average 50 patients per senior HP) will be assigned to the respective senior HP's study arm, thus defining one cluster.

The participating physicians will neither be informed what study arm they belong to nor given specific details of the intervention of the other study arm. Similarly, the patients will not know whether their discharge follows the study (verum) or the "usual" (control) procedures.

The study and control interventions are explained in more detail in subsections 8.1.1 and 8.1.2, and data collection is laid out in sections 9.2 and 9.3. After follow up is completed for all included patients, the HPs in the control group will be debriefed and offered access to and training in the study instrument.

In a process evaluation study carried out in parallel to the RCT we will explore barriers and enablers in terms of acceptance, feasibility and future use of the study intervention, using semi-structured telephone calls or focus group interviews and questionnaires. As a secondary analysis using the original data, a cost analysis will be carried out on the basis of present medication prizes, and costs saved by spared drugs and avoided hospitalizations will be estimated.

## 6.2 Study Duration and Study Schedule

| Time (year)                                     | 2016 | 2017 |   |   | 2018 |   |   |   | 2019 |   |   |   | 2020 |
|-------------------------------------------------|------|------|---|---|------|---|---|---|------|---|---|---|------|
| Quarter                                         | 1-4  | 1-2  | 3 | 4 | 1    | 2 | 3 | 4 | 1    | 2 | 3 | 4 | 1-4  |
| Writing proposals and ethics committee proposal |      |      |   |   |      |   |   |   |      |   |   |   |      |
| Designing intervention                          |      |      |   |   |      |   |   |   |      |   |   |   |      |
| Pilot test                                      |      |      |   |   |      |   |   |   |      |   |   |   |      |
| Adaptation RCT to pilot results                 |      |      |   |   |      |   |   |   |      |   |   |   |      |
| Recruitment RCT                                 |      |      |   |   |      |   |   |   |      |   |   |   |      |
| Data collection RCT                             |      |      |   |   |      |   |   |   |      |   |   |   |      |
| Data analysis RCT                               |      |      |   |   |      |   |   |   |      |   |   |   |      |
| Cost analysis                                   |      |      |   |   |      |   |   |   |      |   |   |   |      |
| Process evaluation study                        |      |      |   |   |      |   |   |   |      |   |   |   |      |
| Communication, dissemination                    |      |      |   |   |      |   |   |   |      |   |   |   |      |
| Reporting, paper writing                        |      |      |   |   |      |   |   |   |      |   |   |   |      |
| Steps, milestones                               |      |      |   |   | A    |   |   |   |      | B |   | C | D    |

Milestones of the project:

- A Study design, protocol and ethics proposal, pilot test of material and procedures in hospital setting
- B Cluster-randomized controlled trial
- C Cost analysis study
- D Process evaluation study (barriers, facilitators among HPs, GPs and patients) and communication/dissemination

## 6.3 Methods of Minimizing Bias

Most of the outcomes are objectively measurable parameters (times and rates) whose collection does not need to rely on the patients' recollection alone but can fall back on systematic documentation at different levels (e.g. GP records). This redundancy of sources can be exploited to increase data quality/reliability, for example in cases of vague or inaccurate information from the patients themselves. The remaining outcomes will be collected either using validated scales (EQ-5D-3L) or tried-and-tested methodology (semi-structured interviews and telephone calls) from previous studies (32, 52).

In order to minimize the risk of mutual interference between clusters in the intervention and control arms, the teaching sessions for senior HPs will be held as separate events, and the participating physicians will be discouraged from discussing aspects of the study with peers who take part in the study as well.

### **6.3.1 Randomization**

Randomization will take place on the level of the participating senior HPs (= clusters) whereby senior HPs working in the same clinic/ward/hospital unit will be jointly allocated to the same study arm. Intern physicians will be assigned deterministically to their senior HPs' study arms. The consecutive inclusion of eligible patients by their HPs will not involve further randomization either as any included patient will be allocated to the trial arm (intervention or control group) of her/his recruiting physician.

Randomization on the cluster level to equally sized treatment arms will be performed using a software random number generator by a member of staff not involved in planning of the study nor the recruitment of participants. Greatest possible balance between the study arms, in terms of the covariates listed in section 5.2, will be achieved through a customized minimization procedure described in more detail in section 7.3.

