| Number of Participants with Rationale: | 
Based on published readmission rates, an exponential survival curve has been modeled. We defined a delay in time to readmission of 25% as relevant. This translates into a difference in medians of 23 days (from 93 to 116 days) and corresponds to a hazard ratio of 0.80 between intervention and control group participants. We assumed a two-sided alpha of 0.05, a power of 80%, an intraclass correlation coefficient (ICC) of 0.02, an overall censoring probability of 40%, and a cluster size of 50 patients per senior HP. Thus, 21 senior HPs and 1’050 patients per arm are needed, i.e. 42 senior HPs and 2’100 patients in total.
 
An interim analysis with 50% of the full sample size is planned in case of poor recruitment success.
                                                                                                                                            |
| Study Duration:                        | Patients will be recruited during 4 months or until the designated number of patients per cluster is reached, and follow up will last for 6 months for each patient.                                                                                                                                                                                                                                                                                                                                                                                                                                                                                                                                                                                                                                                                                                                                           |

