| Statistical Considerations: | 
Pilot test: Mixed methods approach to achieve quantitative (e.g. ratings on a 5-point Likert scale) as well as qualitative (e.g. awareness, perception) results.
 
RCT: Intent-to-treat (ITT) approach. Descriptive statistics to describe the study population. Baseline characteristics will be compared between control and intervention group using t-test, Mann-Whitney U test, <math>\chi^2</math>-test or Fisher's test, according to the type of data. The primary outcomes will be compared using Kaplan-Meier and log rank tests. To assess factors which may affect readmission, Cox regression will be used considering senior HPs as clusters. Determinants associated with a change of the medication will be investigated by exploratory, multivariate regression analysis. For secondary outcomes, parametric (t-tests) or non-parametric tests (<math>\chi^2</math>- and U tests) will be used where appropriate.
                                                                                                                                                                                                                                                                                                            |

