### 7.2 Recruitment and Screening

For the adequate number of HPs and patients to be included in the trial see the sample size calculations in section 11.2.

Different hospitals – including but not limited to the Kantonsspital Baden, Kantonsspital Glarus, Kantonsspital Graubünden Chur (medical clinic), See-Spital Horgen, Spital Lachen, Spital Limmattal Schlieren, Spital Linth Uznach, Spital Männedorf, Kantonsspital Münsterlingen, Spital Muri, Spital Schwyz, Kantonsspital St. Gallen, Stadtspital Triemli Zurich, Stadtspital Waid Zürich, Kantonsspital Winterthur (polyclinic, surgical ward), Spital Zollikerberg, UniversityHospital Zurich (clinics for gastroenterology, pneumology and geriatrics) – will be contacted on the medical management level with detailed written information about the study and an invitation to participate. Should the targeted number of senior HPs be missed due to a low response rate, remainders will be sent out. If, on the other hand, the response exceeds the actual demand then a random selection of senior HPs will be drawn and the remaining respondents will be waitlisted to compensate for potential withdrawals.

The in-hospital recruitment of patients will be performed by HPs and/or nurses; a person responsible for recruitment will be defined in every clinic or ward. The patients' life expectancies and cognitive abilities will be assessed as part of the recruitment process. Patients will be recruited during four months or until the envisaged number of participants per cluster (senior HP) is reached, and follow up will last for six months for each patient.

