### 11.2 Determination of Sample Size

We modeled hospital readmission time by fitting an exponential survival curve on published readmission rates (48, 46) and internal data from the University Hospital Zurich. Extending readmission time by 25% was considered a relevant effect of the intervention. In the fitted model, this translates into an increase of the median readmission time by 23.2 days (from 92.7 days to 116.8 days) and corresponds to a hazard ratio of 0.80 between intervention and control group participants. This is equivalent to a decrease of 18.2% in readmission rates after 30 days (from 20.1% to 16.4%).

Based on this hazard ratio and assuming a two-sided  $\alpha = 5\%$ , a power of  $1 - \beta = 80\%$ , an intraclass correlation coefficient (ICC) of 0.02 as in (18), 40% overall censoring probability and equally sized clusters of 50 patients, we calculated a sample size of 21 clusters and 1'050 individuals per trial arm. Thus, 42 senior HPs and 2'100 patients in total will need to be included in order to observe a relevant effect of the study intervention with sufficient power.

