#### 11.3.2 Primary Analysis

Descriptive statistical methods will be used to describe the study population, including dropouts and losses to follow up. Baseline characteristics of the intervention and control groups will be calculated with corresponding 95% confidence intervals where applicable.

The primary outcome will be compared between groups using Kaplan-Meier and log rank tests. To compare factors which may affect readmission, Cox regression (proportional hazards model) will be used considering hospital clinics/units as clusters. The multivariable model will include patient characteristics as factors as well as all covariates used for balanced allocation of clusters to the study arms, and subgroup analyses may be carried out for such factors or covariates.

For secondary outcomes, parametric ( $t$ -test) or non-parametric tests ( $\chi^2$ - and Wilcoxon test) will be used where appropriate.

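### Senior HPs who share a ward are allocated together but counted as separate clusters, so the 80% power is conditional, and the cluster level is contradictory

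*Protocol*

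**What the plan says.** - **Allocation.** Section 6.3.1 names the senior HP as the cluster and then adds that "senior HPs working in the same clinic/ward/hospital unit will be jointly allocated to the same study arm". Section 6.1 gives the same rule and its reason: several participating HPs might work on one ward, which risks contamination.
- **Sample size.** Section 11.2 works with "equally sized clusters of 50 patients", 21 per arm. Section 6.1 says what a cluster is: "The envisioned number of 42 clusters (i.e. senior HPs; see sample size calculation in section 11.2"). The synopsis agrees, with 50 patients per senior HP.
- **Allocation algorithm.** Section 7.3 generates random schemes for clusters, keeps the best balanced ones and draws one. The only constraint named for generating the schemes is equal arm size. The joint rule for a shared ward is not mentioned.
- **Analysis.** The synopsis states that "Cox regression will be used considering senior HPs as clusters". Section 11.3.2 says that the same model "will be used considering hospital clinics/units as clusters".
- **Not stated.** The protocol gives no expected or maximum number of senior HPs per ward and does not say to which level the ICC of 0.02 applies.

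**The concern.** Two physicians who can never be in different arms are not two randomised units. Wherever they share a ward, the ward is the unit and its patients form one larger cluster. A design effect for clusters of 50 is then too small for those wards, and the planned 2,100 patients carry less information than section 11.2 assumes.

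The inconsistency reaches beyond the sample size. If section 7.3 is followed literally with senior HPs as clusters, a ward can be split between arms, which sections 6.1 and 6.3.1 rule out. The two statements on the Cox model lead to different standard errors for the intervention effect, and no analysis can follow both.

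**Working it through.** **Inputs from the protocol.** Two-sided alpha 5%, power 80%, ICC 0.02, 40% censoring and so 60% events, 50 patients per senior HP, 2,100 patients in total (section 11.2 and synopsis). The effect "corresponds to a hazard ratio of 0.80 between intervention and control group participants".

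**Inputs that the protocol does not give, taken as assumptions.** k is the number of participating senior HPs per ward, from 1 to 3. For a mix of wards, k is the mean taken over senior HPs, so k = 1.25 means that a quarter of them share a ward with one other. ρw is the correlation between patients of different senior HPs in one ward, from 0 to 0.02.

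**Step 1: the plan's own figure.**
- Events (Schoenfeld): 4 × (1.96 + 0.8416)² / (ln 0.8)² = 630.5, rounded up to 631. Freedman's formula gives 636.
- Design effect: 1 + (50 − 1) × 0.02 = 1.98.
- Patients: 631 / 0.6 × 1.98 = 2,082 (Freedman: 636 / 0.6 × 1.98 = 2,099). Either way this is 21 clusters of 50 per arm.
- Power at 2,100 patients: 80.4% (Schoenfeld) or 80.0% (Freedman).

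The stated size is right for 42 independently allocated clusters. It has no slack.

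**Step 2: joint allocation.** The design effect becomes

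DE = 1 + 49 × 0.02 + (k − 1) × 50 × ρw.

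Power is Φ(√E × |ln 0.8| / 2 − 1.96), with effective events E = 2,100 × 0.6 / DE = 1,260 / DE. Patients needed for 80% power are 631 / 0.6 × DE. With ρw = 0.02:

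| k | DE | Effective events | Power at 2,100 | Patients for 80% |
|---|---|---|---|---|
| 1 | 1.98 | 636 | 80.4% | 2,083 |
| 1.25 | 2.23 | 565 | 75.6% | 2,346 |
| 1.5 | 2.48 | 508 | 71.1% | 2,609 |
| 2 | 2.98 | 423 | 63.1% | 3,134 |
| 3 | 3.98 | 317 | 51.0% | 4,186 |

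**Step 3: weaker correlation between HPs of one ward, at k = 2.** ρw = 0.01 gives DE 2.48 and 71.1% power. ρw = 0.005 gives DE 2.23 and 75.6%. ρw = 0 gives DE 1.98 and 80.4%.

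**Step 4: Cox model clustered by senior HP, as in the synopsis.** With k = 2 and the correlation at ward level, the true variance is 2.98 / 1.98 = 1.505 times the one estimated. The nominal cut-off of 1.96 then acts as 1.96 / √1.505 = 1.60, which gives a two-sided type I error of about 11.0%.

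**The case against.** The strongest reply is that the loss of power is conditional, and the protocol does not establish the condition. Section 6.1 says only that HPs might share a ward, and it describes the randomised physicians as those in charge of the units, which also fits one per ward. Joint allocation may be a safeguard for a few shared wards. This stands. A reader might infer that 80% power is not delivered at all, but the documents do not show that: with k = 1 or ρw = 0 the plan's figure is correct.

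A reader might also divide 42 senior HPs by the hospitals listed in section 7.2 and infer about two per unit. That does not follow. The hospitals "will be contacted on the medical management level with detailed written information about the study and an invitation to participate", the list is expressly open, no unit is named for 14 of the 17, and section 6.1 foresees senior HPs in different wards of one hospital.

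The figures at ρw = 0.02 are at the upper end of the assumed range, since they let the full ICC hold between different HPs of a ward. Basing the design effect on events per cluster (50 × 0.6 = 30) instead of patients would also soften the loss: k = 2 gives 1 + 59 × 0.02 = 2.18 and about 77% power. The plan did not use that variant, which would need only 17 clusters per arm.

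Finally, section 11.3.2 already uses the clinic or unit as the cluster. The 11% belongs to the Cox model in its synopsis wording. A reader might carry it over to the primary comparison, but that is a log-rank test, for which the protocol names no cluster level. None of this removes the conflict between the allocation rule, the sample size and the two analysis statements.

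**Conclusion.** The point holds in conditional form. The allocation rule makes the ward the randomised unit wherever senior HPs share one, while the sample size treats every senior HP as independent. The stated 80% is valid only with one senior HP per ward, or with no correlation between patients of different HPs in a ward. With ρw = 0.02, power falls to about 76% if only a quarter of the senior HPs share a ward with one other, and to about 63% if all do. With ρw = 0.01 the latter figure is about 71%. The number of HPs per ward and the level of the ICC are assumptions throughout.

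The contradictory cluster level in the Cox model and the missing joint rule in section 7.3 are errors in the text and depend on no assumption. The size of the type I error does: about 11% at two HPs per ward, with the correlation at ward level.

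**What to change.** - Define the cluster as the jointly allocated clinic or ward in sections 6.1, 6.3.1, 7.3 and 11.2 and in the synopsis, in line with section 11.3.2.
- Write joint allocation into the algorithm of section 7.3, so that wards and not single senior HPs are drawn.
- Delete the synopsis statement that takes senior HPs as clusters in the Cox model.
- State in section 11.2 the expected or maximum number of senior HPs per ward and the level to which the ICC applies, and restate the power for them.
- Where response exceeds demand and section 7.2 already foresees a random selection, prefer one senior HP per ward.

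These are text changes, best made before randomisation. The downside is a less favourable stated power. No patients need be added if that power is accepted. Keeping 80% with shared wards would need more patients, for example 3,134 (32 senior HPs per arm) at two HPs per ward and ρw = 0.02. Preferring one HP per ward helps only if enough wards respond.
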